### Procedure

Thirteen therapists in six Dutch mental health care institutions will select all patients in their caseload that meet the inclusion criteria. They will answer four screening questions concerning these patients’ metacognitive abilities on a 10 point scale (see Section Screening for the screening questions). The therapists approach the patients that score below the cut-off of the screening and ask them if they are interested in participation. The names of the interested patients will be coded by the therapist. Out of these coded names a random selection will be chosen by the researchers to prevent selection bias. The selected coded names will be transferred back to the therapists, who will then provide the contact information of these patients to the researcher and will inform the patients that an assessor will approach them. The assessor will call the patient and answer any questions the patient may have about the study. Every participant has a two-week period to consider participation. If the patient is still willing to participate after this period, an assessor will make an appointment for an intake to confirm that the patient fulfills all of the study’s inclusion criteria. The intake will take approximately 1,5 hours. Patients that are included in the study will be randomly allocated to the treatment condition (MERIT) or treatment as usual (TAU). The randomization is conducted separately for each center and procedures will start directly after the first participants are included. Randomization will be done by a party independent from the trial research team. Results of the randomization process will be passed on to the onsite therapists. Block randomization will be used to ensure that the number of patients will be balanced over condition. Assessors will be blind to the subject’s condition. Rater blinding will be verified after the assessment. For therapists, it is of course not possible to be blind for condition. After assignment to intervention or control condition, the assessor plans a second appointment with the patient for baseline assessment. A research assistant, blind to treatment or control condition, who is not involved in the patient's treatment, will carry out this assessment. This assessment will take approximately 1.5 hours. Thereafter, the individual treatment will start. Onsite clinical psychologists that have partaken in the three-day MERIT training will provide the intervention. Participants in the control condition will receive treatment as usual (TAU). After forty sessions of treatment or forty weeks in the control condition, the assessment will be repeated (post-treatment). Follow-up assessment will take place six months after completion of the intervention.

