### Research aims

Primary objective of this study is to investigate whether Metacognitive Reflection and Insight Therapy improves metacognitive abilities in people with schizophrenia. Secondary objective is to examine whether improvements in metacognitive capacity lead to improvements in quality of life, social functioning, depression, symptoms, stigma sensitivity and work readiness. Neurocognition is adopted in the assessment as well, as it may function as a mediator between metacognition and functioning. A cost-effectiveness analysis will be performed at the end of the study.

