### Participants/setting

Participants in the study are people with schizophrenia or schizoaffective disorder and impaired metacognitive abilities. A total of 120 participants will be included from six mental health care institutions in the Netherlands. Thirteen therapists who work in these facilities will be trained to give the therapy.

Inclusion criteria are:

Impaired metacognitive skills, as measured by the Metacognition Assessment Scale (MAS-A);

Diagnosis of schizophrenia or schizoaffective disorder, according to DSM-IV-TR criteria;

Being able to give informed consent;

18 years or older;

No change in medication in the past thirty days.

Exclusion criteria are:

Acute psychosis (mean score of PANSS positive symptoms >4);

Co-morbid neurological disorder;

Substance dependence (not substance abuse as measured with the MINI Plus);

Impaired intellectual functioning (IQ <70)

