**Work readiness***Work Readiness Questionnaire (WoRQ)*[48]. This questionnaire is filled in by the therapist of the client and has seven items designed to capture the patient's readiness to work as reflected by current capacity to initiate and maintain a useful activity. The items are rated to provide graded measurements, i.e., “strongly agree”, “agree”, “disagree” or “strongly disagree”. Next to these seven items it contains a final dichotomous work readiness judgment.

#### 

**Neurocognition***Nederlandse Leestest voor Volwassenen (NLV)*[49]. The NLV tests the pronunciation of irregularly spelled words and is used to determine premorbid intelligence.

*Trailmaking test A&B (TMT)*[50]. The TMT provides information on visual search, scanning, mental flexibility speed of processing and executive functions. It is part of the Halstead–Reitan Battery
[50]. The TMT consists of two parts. Part A requires an individual to draw lines sequentially connecting 25 encircled numbers distributed on a sheet of paper. Task requirements are similar for Part B except the person must alternate between numbers and letters (e.g., 1, A, 2, B, 3, C, etc.). The score on each part represents the amount of time required to complete the task
[51].

*Digit Symbol Test* (part of the Wechsler Adult Intelligence Scale
[52]). This test evaluates the recognition and recoding of visual information. The test consists of several rows of paired boxes with a digit in the top box and an empty space in the box below. At the top of the page is shown which symbols are paired to the digits. The participant has to fill in as many symbols in the empty boxes within 90 seconds.

#### 

**Cost-effectiveness***EuroQol (EQ-5D)*[53]. This questionnaire contains five scales: self care, mobility, usual activities, pain/discomfort and anxiety/depression. The participant has to rate his/her health as it is on the day of the interview, using five levels: “no problem” “slight problems” “moderate problems”, “severe problems”, “unable”/”extreme problems”
[54].

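### Baselines for five of the six secondary domains are scheduled after randomisation, once therapists are told the arm; the primary baseline is not affected

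*Protocol article*

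**What the plan says.** The Procedure section gives this order: intake, randomisation, communication of the result, baseline visit, treatment. On communication it says "Results of the randomization process will be passed on to the onsite therapists". On the next step it says "After assignment to intervention or control condition, the assessor plans a second appointment with the patient for baseline assessment". It describes the person who carries out the baseline visit as "A research assistant, blind to treatment or control condition, who is not involved in the" patient's treatment, and it says of therapists: "For therapists, it is of course not possible to be blind for condition".

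Table 1 agrees. The MINI-Plus, IPII, MAS and PANSS are in the intake column, before randomisation. The Faux Pas test, empathic accuracy test, IRI, QIDS-SR, BCIS, ISMI, MANSA, Time Use, WoRQ, NLV, Trailmaking, Digit Symbol, TiC-P and EQ-5D are in the baseline column, after it.

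Research aims names the secondary outcomes as "improvements in quality of life, social functioning, depression, symptoms, stigma sensitivity and work readiness". The Assessment section describes the QIDS-SR, BCIS, ISMI and MANSA as self-report or self-rating, and has the WoRQ completed by the patient's therapist. The Analysis section compares scores before treatment, after treatment and six months later, with condition as the independent variable and dummy variables and their interactions as fixed effects.

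On intelligence, the exclusion list contains "Impaired intellectual functioning (IQ <70"), and the Procedure section uses the "intake to confirm that the patient fulfills all of the study’s inclusion criteria". The NLV, which "is used to determine premorbid intelligence", appears in Table 1 only from the baseline column onward.

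**The concern.** A baseline protects a before/after comparison only if the arm cannot have influenced it. Here most pre-treatment scores are collected when at least one party knows the arm. The blinded research assistant guards the tests that the assistant scores, but cannot blind a therapist who fills in a form or a patient who rates their own mood, stigma or quality of life.

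What is at stake is the set of secondary contrasts. A baseline moved by knowledge of the arm goes into the condition-by-time term as if it were a treatment effect, with the opposite sign. In addition, a patient who withdraws between allocation and the baseline visit has been randomised but has no baseline on these instruments.

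The intelligence criterion raises a related question. If the only listed test that bears on it follows randomisation, it is unclear how the criterion is settled beforehand.

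**Working it through.** **1. How much of the battery is affected.** Counting Table 1 rows that have a pre-treatment measurement and are repeated later:

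- before randomisation: IPII, MAS, PANSS = 3
- after randomisation: the 14 instruments in the baseline column
- share after randomisation: 14/17 = 82%

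By secondary domain:

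| Domain | Instrument | Baseline relative to randomisation |
|---|---|---|
| Quality of life | MANSA | after |
| Social functioning | Time Use | after |
| Depression | QIDS-SR | after |
| Symptoms | PANSS | before |
| Stigma | ISMI | after |
| Work readiness | WoRQ | after |

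Five of six follow randomisation.

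**2. Who could be influenced.** The 14 instruments are not equally exposed:

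- 7 patient questionnaires (IRI, QIDS-SR, BCIS, ISMI, MANSA, TiC-P, EQ-5D): exposed if the patient knows the arm
- 1 therapist-completed form (WoRQ): exposed whether or not the patient knows, taking the patient's therapist to be one of the onsite therapists who receive the result
- 1 structured interview (Time Use): the interviewer is blind, but the answers come from the patient
- 5 performance tests (Faux Pas, empathic accuracy, NLV, Trailmaking, Digit Symbol): unlikely to move

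**3. How a shift enters the estimate.** Let b be the arm difference at baseline, in SD units, caused by knowledge of the arm, with no effect on later scores. Let r be the baseline–outcome correlation.

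- Change from baseline: bias of size b.
- Baseline-adjusted: bias of size r × b.

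The documents give neither b nor r. Over an assumed b of 0.1 to 0.3 and r of 0.3 to 0.7, the bias is 0.1 to 0.3 SD for change scores, and 0.3 × 0.1 = 0.03 to 0.7 × 0.3 = 0.21 SD with adjustment. The effect size used for the sample size is 0.5. A shift of 0.15 is 0.15/0.5 = 30% of it, or 0.075/0.5 = 15% after adjustment at r = 0.5.

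**4. What that does to the test.** The plan has no figure of its own here to reproduce. I take its 48 per group as given, two-sided alpha 0.05, and assume r = 0.5. Then:

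- SD of change = √(2(1 − r)) = 1.000
- residual SD after adjustment = √(1 − r²) = 0.866
- noncentrality = (bias/SD) × √(48/2) = (bias/SD) × 4.899
- rejection rate from the noncentral t with 94 df (93 df for the adjusted model gives the same rounded results)

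| b | Analysis | Noncentrality | Two-sided rejection under the null |
|---|---|---|---|
| 0.15 | change | 0.15 × 4.899 = 0.735 | 11.2% |
| 0.15 | adjusted | (0.075/0.866) × 4.899 = 0.424 | 7.0% |
| 0.20 | change | 0.20 × 4.899 = 0.980 | 16.3% |
| 0.20 | adjusted | (0.10/0.866) × 4.899 = 0.566 | 8.7% |

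**5. Direction.** If hope makes MERIT baselines look better and disappointment makes TAU baselines look worse, MERIT has less apparent room to gain and TAU has more. At b = 0.15 on change scores, the 11.2% then splits into 10.9% favouring TAU and 0.4% favouring MERIT (2.5% each without a shift; the parts are rounded). At b = 0.20 the split is 16.1% and 0.2%. For the WoRQ, which way an unblinded therapist would lean is unknown.

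**6. The intelligence criterion.** Set side by side, Participants/setting excludes IQ below 70, the Procedure section settles eligibility at intake, and Table 1 has no intelligence measure at selection or intake. Both tests related to intelligence (the NLV and Digit Symbol, a Wechsler subtest) follow randomisation. The Assessment section does not say that the NLV decides the exclusion.

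**The case against.** The strongest case on the other side has six parts.

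- **The primary objective is untouched.** The MAS on the IPII is taken before randomisation. This stands and limits the point to secondary outcomes.
- **Patients may not know their arm.** The text says only that therapists are told. This stands for the self-reports, where influence is possible rather than shown. It does not help the WoRQ.
- **A reader might infer from the 11% and 16% that false claims of benefit are inflated.** The documents do not support that. The shifts are assumed, and under the most natural mechanism almost all the excess favours TAU, so the likelier harm is an underestimated benefit.
- **A reader might infer that the bias cannot be adjusted away.** That is too strong. Adjustment reduces it to r × b, and a direct comparison of post-treatment scores does not use the baseline. A remainder persists in any analysis that does use it.
- **Missing baselines need not be fatal.** A multilevel model can use incomplete series, and 20% dropout is allowed for. This largely stands, although Sample size calculation also says that dropouts will be excluded from the analysis.
- **A reader might infer that ineligible patients will be discovered and removed after allocation.** No text says that the NLV decides the exclusion or that such removals are planned. Therapists preselect from their own caseload, so IQ might come from records, and a condensed article may leave that out. What stands is a request for clarification.

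**Conclusion.** The order of steps is a real but limited weakness. Five of six secondary domains have a post-allocation baseline, and for the WoRQ the rater is someone the protocol itself says cannot be blind. The article gives no reason for this order.

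The size of any bias cannot be determined from the documents. With an assumed 0.15 SD shift, r = 0.5 and 48 per group, the two-sided error rate rises from 5% to about 11% for change scores and about 7% with baseline adjustment. The direction is uncertain. The self-report part rests on patients learning their arm before the visit; the WoRQ part does not. The primary outcome and the PANSS are unaffected. The intelligence criterion is a secondary question about where eligibility is checked, not a demonstrated error.

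**What to change.** Complete the whole baseline battery, including the WoRQ, before the independent party generates or releases the allocation. Amend the Procedure section and Table 1 so that the randomisation step follows the baseline column. Withdrawals before the baseline visit then occur before the arm is known, and every patient whose arm is known has a baseline.

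State in the article or full protocol how IQ below 70 is established. If the NLV is the test used, take it at intake so that nobody is excluded after randomisation.

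The cost is a short delay before allocation, a small amendment and a table edit. No instrument or visit is added and the sample size does not change.

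The change does not cure the therapist's unblinded WoRQ ratings at post-treatment and follow-up, which should be acknowledged when that outcome is interpreted.

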
### Materials

A summary the design of the study and all materials is provided in the table below (Table 
1).

**Table 1 T1:** Study design

**Instrument:**	**Selection**	**Intake**	**Assessment to condition**	**Baseline measures**	**Intervention**	**Post- treatment**	**Follow-up**
Four questions for the therapist	X						
MINI-PLUS		X					
IPII		X				X	X
MAS- NL		X				X	X
PANSS		X				X	X
Randomization			X				
Faux Pas test				X		X	X
Empathic accuracy test				X		X	X
IRI				X		X	X
QIDS-SR				X		X	X
BCIS				X		X	X
ISMI				X		X	X
MANSA				X		X	X
Time-use				X		X	X
WorQ				X		X	X
NLV				X		X	X
Trailmaking A&B				X		X	X
Digit symbol				X		X	X
Tic-P				X		X	X
EQ5D				X		X	X
MERIT therapy or control					X		

#### Metacognitive reflection and insight therapy (MERIT)

The experimental condition will receive the Metacognitive Reflection & Insight Therapy [based on 26]. This manual-based individual psychotherapy aims to stimulate the four elements of metacognition. The treatment protocol is not a step-by-step program, but is target-driven. The therapist tries to elicit a narrative; a personal story of the patient. In this personal narrative, the therapist looks for targets; signs of metacognition. Is the patient aware of his thoughts? Can he reflect on those thoughts and on the thoughts of others? The levels of MAS-A are used here to classify the different levels of metacognitive functioning. The therapist adjusts his interventions according to the level of metacognition of the patient and stimulates the patient to perform ever more complex metacognitive tasks. The therapy will consist of 40 times 45 minutes of individual therapy sessions. The treatment protocol has been translated into Dutch by the research team. Every participating therapist will follow a three-day training in the therapy provided by PL, the first author of the therapy manual. The most important aspects of the therapy are summarized in the Therapist Metacognitive Adherence Scale (T-MAS, see Table 
2). The eight core items of the T-MAS are explained in detail in the protocol and the therapists will practice these elements in the training. The therapist has to give him/herself a score on a ten-point scale on the items of the T-MAS after every therapy session. In this way the therapist can monitor his/her own adherence to the aspects of the therapy. Transcripts of sessions will be selected at random and will be scored by independent assessors with the T-MAS, to monitor if the therapist follows the elements of the therapy correctly. Every other week each therapist will receive supervision by the developer of the therapy, PL, using Skype. In these sessions the adherence to the therapy elements and the T-MAS scores will be discussed and the therapists receive supervision on how they conduct the therapy.

**Table 2 T2:** The therapist metacognitive adherence scale

Openness to the patient’s agenda at the session outset and throughout the session.	1	2	3	4	5
Offer of the therapist’s thoughts/perceptions regarding the patient’s behavior in the session.	1	2	3	4	5
Details of a narrative episode are elicited.	1	2	3	4	5
A psychological problem or dilemma is framed as something to be discussed.	1	2	3	4	5
Reflection on the interpersonal processes during the session is elicited.	1	2	3	4	5
Reflection on progress/course of the session is elicited at various times during the session or at session’s end.	1	2	3	4	5
The patient is stimulated to engage in metacognitive acts with interventions that are appropriate to patient’s capacity for self-reflectivity and/or awareness of the mind of the other.	1	2	3	4	5
The patient is stimulated to engage in metacognitive acts with interventions that are appropriate to patients’ capacity for metacognitive mastery.	1	2	3	4	5

**Key:** 1. Absent; 2. Intermittent moments in which basic competency is present; 3. Fully adequate or competent throughout; 4. Fully adequate with some periods of exceptional performance; 5. Consistently exceptional performance.

#### Screening

On-site therapists will screen all patients in their caseload that meet the inclusion criteria; they will answer four screening questions concerning each of these patients’ metacognitive abilities:

– To what extent is the patient able to think about his/her own thoughts?

– To what extent is the patient able to explain his/her thoughts and feelings in an adequate manner?

– To what extent is the patient able to explain the thoughts and feelings of others in an adequate manner?

– To what extent is the patient able to use his/her understanding of his/her own thoughts and feelings and the thoughts and feelings of others to react adequately during stressful events?

The therapists will answer these questions on a 10-point scale, 10 meaning excellent, 0 very poor. They select all the patients that score below 6 on two or more of the four questions, who will be approached for participation.

#### Intake

**Diagnosis***M.I.N.I Plus Interview*[37]. This structured interview is used to confirm a diagnosis of schizophrenia or schizoaffective disorder. It is designed to detect Axis I diagnoses of the DSM IV-TR. The interview is divided into 26 sections; each section concerns a diagnostic category. At the end of every category the interviewer can determine whether the patient fulfills the diagnostic criteria for the diagnosis of the particular section.

#### 

**Metacognition***Indiana Psychiatric Illness Interview*[38]. This interview, which consists of five open questions, was developed with the goal of eliciting the life story and illness history of the patient. The MAS-A can be scored on the resulting transcript.

*Metacognition Assessment Scale*[10,11]. The MAS-A consists of four scales. The cutoff points for each scale: Selfreflectivity: below 5.5, Understanding the other’s mind: below 4.5, Decentration: below 2, Mastery: below 4.5. When the patient gets a score below cut off on three or more scales, metacognitive deficits are prominent and the patient meets the inclusion criteria.

#### 

**Symptoms***Positive and Negative Syndrome Scale*[39]. This structured interview consists of thirty items, each ranging from one to seven. The items fall into three subscales: positive symptoms, negative symptoms and general symptoms.

#### Assessment

**Metacognition***Beck Cognitive Insight Scale (BCIS)*[40]. This self-report questionnaire evaluates the reflectiveness and overconfidence in the interpretation of experiences of the patient. It consists of fifteen items, six items represent the self-certainty subscale, nine items represent the self-reflectiveness subscale.

*Faux Pas Task*[41]. This task consists of ten stories, describing interpersonal, everyday situations. Some of these stories contain a ‘faux pas’: a speaker in the story says something without considering if it is something that the listener might not want to hear. The patient has to detect these mistakes.

*Empathic Accuracy Task (EAT)*[42]. This task consists of ten videos of people who tell a personal story. The participant has to rate the mood of the person in the video continuously on a 9 point scale.

*Interpersonal Reactivity Index* (IRI)
[43]. This questionnaire exists of 28 statements. The participant has to indicate whether the statement applies to him/her on a six point scale.

#### 

**Depression***The Quick Inventory of Depressive Symptomatology Self Report (QIDS-SR)*[44]. This self-report questionnaire consist of sixteen items, measuring depressive symptoms according to the DSM-IV in the week before assessment.

#### 

**Stigma***The Internalized Stigma of Mental Illness Scale (ISMI)*[45]. This is a self-rating questionnaire with 29 questions designed to measure the subjective experience of stigma. It consists of five subscales: Stereotype Endorsement, Perceived Discrimination, Social Withdrawal, Stigma Resistance and Alienation.

#### 

**Quality of life***Self-rating Manchester Short Assessment of Quality of Life (MANSA)*[46]. This questionnaire consists of four objective questions and twelve subjective questions. These subjective questions assess satisfaction with life as a whole, job, financial situation, number and quality of friendships, leisure activities, accommodation, personal safety, people that the individual lives with, sex life, relationship with family, physical health and mental health. It is a self-report, 16 Likert-scale item measure.

#### 

**Social functioning***Time Use*[47]. This structured interview investigates the way in which the patient spends his/her time and makes a detailed account of his/hers: employment, education and training, voluntary work, leisure activities, hobbies, child care, housework and chores.

#### 

**Work readiness***Work Readiness Questionnaire (WoRQ)*[48]. This questionnaire is filled in by the therapist of the client and has seven items designed to capture the patient's readiness to work as reflected by current capacity to initiate and maintain a useful activity. The items are rated to provide graded measurements, i.e., “strongly agree”, “agree”, “disagree” or “strongly disagree”. Next to these seven items it contains a final dichotomous work readiness judgment.

#### 

**Neurocognition***Nederlandse Leestest voor Volwassenen (NLV)*[49]. The NLV tests the pronunciation of irregularly spelled words and is used to determine premorbid intelligence.

*Trailmaking test A&B (TMT)*[50]. The TMT provides information on visual search, scanning, mental flexibility speed of processing and executive functions. It is part of the Halstead–Reitan Battery
[50]. The TMT consists of two parts. Part A requires an individual to draw lines sequentially connecting 25 encircled numbers distributed on a sheet of paper. Task requirements are similar for Part B except the person must alternate between numbers and letters (e.g., 1, A, 2, B, 3, C, etc.). The score on each part represents the amount of time required to complete the task
[51].

*Digit Symbol Test* (part of the Wechsler Adult Intelligence Scale
[52]). This test evaluates the recognition and recoding of visual information. The test consists of several rows of paired boxes with a digit in the top box and an empty space in the box below. At the top of the page is shown which symbols are paired to the digits. The participant has to fill in as many symbols in the empty boxes within 90 seconds.

#### 

**Cost-effectiveness***EuroQol (EQ-5D)*[53]. This questionnaire contains five scales: self care, mobility, usual activities, pain/discomfort and anxiety/depression. The participant has to rate his/her health as it is on the day of the interview, using five levels: “no problem” “slight problems” “moderate problems”, “severe problems”, “unable”/”extreme problems”
[54].

*TiC-P*[55]. This is a questionnaire. The first part consists of medical resource items, including: contacts within the mental healthcare sector, self-help groups, contacts with general healthcare providers, and the use of medication. The patient has to indicate whether he/she makes use of these items and if yes, how many times. Depending on the relevance for the target population, the questionnaire allows adding or leaving out specific items of resource utilization. Part two consist of the Short Form-Health and Labour Questionnaire (SF-HLQ) an instrument that collects data on productivity losses due to health problems. This part measures absence from work and reduced.

